#### Short physical performance battery (SPPB)

It assesses physical performance on the basis of three criteria by testing balance, walking speed, and chair-raising abilities. This scale is used for the inclusion of participants (40).

#### Assistive technology device predisposition assessment (ATDPA-5 – scales B and E)

This scale assesses the person’s need for technology. It has two parts. A part on the individual with 9 items assessing functional capacities and 11 items on well-being. These first 20 items are to be filled in on a five-point Likert scale, ranging from 1: poor/not satisfied to 5: excellent/very satisfied. Finally, this last part also assesses personal and psychosocial characteristics. There is no threshold value for these last items. The second part deals with technological tools with 12 items, highlighting their expectations in terms of benefits toward three technological tools. There is no threshold for this scale, but the scores range from 0 to 60 (sum of the statements). The tool with the highest score is considered the most important. This scale is used at the beginning of the experiment. Only parts B and E will be used and adapted for the project (68).

#### Big five inventory – 10 (BFI-10)

The BFI-10 (69) is a concise 10-item scale designed to assess the Big Five personality traits: extraversion, agreeableness, conscientiousness, emotional stability, and openness. Participants rate each item on a scale ranging from 1 (disagree strongly) to 5 (agree strongly).

#### Short food frequency questionnaire (FFQ)

FFQ serves as a scale to estimate the frequency of daily food intake over a specified period. This questionnaire seeks information on how often certain foods are consumed (e.g., once daily, once or twice a week, and once or twice a month) and the approximate serving size. It is designed to capture data on habitual food intake rather than quantifying the exact nutrient amount ingested. In Europe, partners will utilize the scale developed by Robinson et al. (67).

#### eHealth scale

The eHEALS is an 8-item assessment designed to gauge eHealth literacy, measuring consumers’ collective knowledge, comfort, and perceived skills in finding, evaluating, and applying electronic health information to address health-related issues.

#### Revised UCLA loneliness scale version 3

The revised UCLA Loneliness Scale Version 3 is a dependable and consistent questionnaire-based measure designed to assess trait loneliness (66). Comprising 20 items, respondents rate each item on a scale from 1 (never) to 4 (often), yielding a loneliness score ranging from 20 to 80. A higher score on the scale indicates a greater level of trait loneliness.

#### System usability scale (SUS)

The System Usability Scale (SUS) stands as a reliable tool for assessing usability, featuring a 10-item questionnaire with five response options ranging from ‘strongly agree’ to ‘strongly disagree’. This versatile scale enables the evaluation of a diverse range of products and services, spanning hardware, software, mobile devices, websites, and applications. Its ease of administration to participants, suitability for small sample sizes, and ability to effectively distinguish between usable and unusable systems contribute to its widespread applicability and reliability in usability assessments.

#### User experience questionnaire (UEQ)

The questionnaire incorporates scales that provide a comprehensive assessment of the user experience. It encompasses classical usability dimensions such as efficiency, perspicuity, and dependability while also evaluating user experience aspects, such as originality and stimulation. This holistic approach ensures a well-rounded understanding of the overall user experience, considering both functional and experiential aspects of interaction with the system or product.

#### User experience questionnaire + (UEQ+)

To measure the user experience of the voice interaction in particular, additional scales such as response behavior or response quality from the UEQ+ can be added.

#### Affinity for technology interaction (ATI)

The scale, evaluated in 2019 from the study by Franke et al., measures a person’s interaction-related affinity with technology. It consists of nine items and uses a six-point Likert scale ranging from 1 = completely disagree to 6 = completely agree (71).

#### Physical and leisure activity checklist

An *ad-hoc* checklist has been developed to collect information on engagement in leisure and physical activities of the participants during the e-VITA trial. It contains questions, which are rated on a six-point Likert scale, about common physical and leisure activities and a section to report the personal practices and frequency put in place by the participants.

#### Scales at T0 and T2 for the control group

These two scales are necessary to better understand our participants. The scale at T0 focuses on the dimensions of daily life, social, and prevention. The T2 scale focuses on the participants’ feelings, following the experiment, their experience with the information booklet and its usability, and their well-being.

### Risk–benefit analysis

During the use of robotic platforms or, in wider terms of technological applications, a general difficulty in distinguishing between the artificial world and reality may occur. Especially, in the case of vulnerable older adults, the interaction may generate a general feeling of attachment and dependency. To avoid this, e-VITA has been designed to not look like a human but to preserve artificial aesthetics, as suggested by the guidelines. In addition, during the first contact with the participants but also during all the interventions, researchers will be in contact with the users, continuously stimulating awareness about the technological applications and monitoring the appropriateness of the use of the solution in terms of autonomy of the users, specific needs, and personal preferences. In particular, following the recommendations provided by Comitato nazionale di bioetica (Cnb) of the Ministry of Health (71) on robotics and roboethics, the exit strategy of e-VITA will aim to:

promote adequate experimentation of robotics in the field assistance in order to ensure conditions for the physical and psychological integrity of the user, explaining the risks and benefits, which was highlighted also in the informed consent;ensure both equitable access to robotic and general technologies and the use of robots to assist and not to replace humans, in order to avoid delegating the irreplaceable human task of care and assistance to the machine;the need that the introduction of robotics in medicine entails always the real consideration of the benefits, of the complexity of the change complete with the structure of the services and the economic burden that this entails.

There is a risk that the older adults may wish to stop interacting with the technological devices (for example, because they do not like the NAO robot). In this case, the experiment will be immediately stopped and terminated.

The presence and use of technological devices (virtual coaches and sensors) in participants’ homes can be a source of discomfort. Therefore, pre-studies with end-users (older adults) and stakeholders (informal carers, health professionals, family, NGOs etc.) have been carried out in order to propose virtual coaches that meet the needs of older adults. In addition, safety procedures were also designed to limit the risks as much as possible.

To protect the safety of participants:

participants will be informed about the appropriate use of the virtual coach or technological device (e.g., cannot lean on the technological device or make a movement that could destabilize it);the researcher will train the participant in the use of the sensors and be available in case of problems;the technological devices will be placed in the participant’s home in a configuration that allows them to be used safely.

In the case of adverse events occurring despite the precautions described above:

participants will be instructed to press the “off” button on the device or to disconnect it, according to the instructions in the user manual;participants will call the researcher, who will assist the participant in case of problems;participants will be able to call the researcher, who will come and ensure that no damage has been caused to the participants or to any other person.

To mitigate potential technological dependency, especially with humanoid or theomorphic robotic systems, participants will undergo instruction and training for the appropriate and limited use of virtual coaches. Researchers will maintain contact with participants to ensure proper guidance. Despite the existing risk, it is crucial to acknowledge that current technology has not reached the level of sophistication, which is necessary for natural human–robot interaction. Presently, there is limited progress in developing coaching devices that are capable of minimal social interaction, involving emotional and psychological engagement in controlled conditions. However, precautions, including the provision of adequate training and daily support/monitoring by researchers, are essential to safely use coaching devices in emotional, social, and psychological terms and prevent potential future dependency.

Finally, if after the experimentation, the participants would ask for a longer use of the system, they will be asked to be involved in similar studies, to ensure the continued use of the technology. Moreover, after the end of the study, the opportunity to receive personalized support on everyday technology will be offered to the participants about eHealth literacy and similar solutions for health.

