**Methods:**

This study will recruit 240 healthy subjects aged 65 years and older. Participants will be assigned to an experimental group that will receive the e-VITA system or to the control group that will receive an information booklet only. The primary outcome measure is the person's quality of life (QoL). Data will be collected at baseline, 3 months after the trial, and at the end of the trial, after 6 months.

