#### Sample size determination

In the study by Summers et al. (42), the EuroQol 5 dimensions (EQ 5D) was evaluated in two groups of older adults with physical pre-frailty conditions. EQ 5D, a test widely used to measure health status-related quality of life, was used to calculate the sample size. Assuming an overall sample size of 220 subjects (110 cases and 110 controls), 2 repeated assessments (baseline and follow-up), a significance level of 0.05, power of 90%, a correlation among repeated measures of 0.5, and a non-sphericity correction ε of 1 in an ANOVA model within-between interactions, the achieved effect size for this study is 11% (corresponding to a small effect size in a coherent way with the literature). Even factoring in a dropout rate of 10%, the total number needed would be 240 subjects, evenly divided into 120 cases and 120 controls. The hypothesis is that this sample size is more than adequate to detect variations in secondary outcomes. For these secondary outcomes, a treatment effect size is assumed to be similar to or even greater than the one identified for the primary outcome.

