**Figure 1 fig1:**
[figure not shown]
Flowchart of the patient selection.

In total, 120 subjects will be enrolled in the experimental group and will receive the e-VITA platform composed of a virtual coach, several sensors for monitoring, and a smartphone to use at home.

The control group will receive only the booklet with nutritional, cognitive, and physical suggestions.

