### Outcome measures

All outcomes will be measured following a standardized operating procedure. The primary endpoint of the study is constituted by the improvement in the quality of life after the use of the e-VITA system, to be measured through the EQ-5D-5L, after 6 months of training.

The secondary endpoints encompass: (1) adherence to the coaching intervention, measured by the frequency of technological device usage, and collected through semi-structured interviews and technical data; (2) usability and the user experience of the overall system assessed using the System Usability Scale (SUS) (62) at both the midpoint and the conclusion of the experiments, along with the User Experience Questionnaire [UEQ (63) and UEQ+ (64)] in the middle and at the end of the experiments; (3) improvement in eHealth literacy, to be addressed through the eHealth Literacy Scale (eHEALS) (65), social connectedness through the UCLA Loneliness scale (UCLA) (66), nutritional state through the short version of Food Frequency Questionnaire (FFQ) (67) to estimate the frequency of daily food intake over a period, cognitive status, through Montreal Cognitive Assessment (MoCA) (39), psychological mood through the Geriatric Depression Scale (GDS) (40), functional status through Short Physical Performce Battery (SPPB) (41), participation to leisure activities through an *ad-hoc* checklist; meets the participant’s objectives through ADTPA-5 (scale B and E adapted) (68). A semi-structured interview will be used to complement the information collected by questionnaires, focusing on acceptability, attitude, usability, and cost–benefit analysis; other questionnaires will be used to better understand our participants’ sociodemographics questionnaire, Clinical Frailty Scale (CFS) (38), Big Five Inventory – 10 (BFI-10) (69), and Affinity for Technology Interaction (ATI) (70).

Table 3 presents a concise overview of all collected data and their respective collection time points.

**Table 3 tab3:** Schedule of assessment and outcome measures.

Dimension	Scale	R	T0	T1	T2
Clinical frailty scale	CFS	X			
Cognitive status	MoCA	X			X
Psychological status	GDS	X			X
Physical capacity	SPPB	X			X
Overall health status	Clinical anamnesis	X			
General information	Socio-demographics questionnaire	X			
Quality of life	EQ-5D-5L		X		X
Goals and expectation	ATDPA-5 (Scale B and E)		X		X (Scale B)
eHealth literacy	eHEALS		X		X
Social connectedness	UCLA		X	X	X
Personality	Big Five Inventory – 10 items		X		

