#### Data collected by the researchers

The first step of the data analysis will deal with the description of the sample. Continuous variables will be reported as either mean and standard deviation or median and interquartile range based on their distribution (assessed using the Kolmogorov–Smirnov test). Categorical variables will be expressed as an absolute number and percentage. Comparison of baseline measurements between groups will be evaluated by unpaired t-test (for normal distribution), Mann–Whitney U tests (for non-normal distribution), or chi-square tests (for categorical variables). Within each group, independent and dependent variables will be compared between the pre-conditions and post-conditions using the same tests as appropriate. The treatment effect on the outcome variables will be evaluated by using repeated measures ANOVA, in order to compare the changes over time in the outcome measures between the intervention group and control group. Moreover, a linear regression model on the outcome variation between baseline and follow-up will be estimated in order to evaluate the effect of the treatment adjusted for all potential confounders. For the analysis of the results, the two types of subjects, stratified according to the MoCA cutoff (score ≥ 26 for cognitively healthy subjects, score 22 to 25 for subjects with mild cognitive decline), will be considered separately. Descriptive statistical analyses will be performed on the quantitative data with SPSS or R studio.

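### The rule for participants who want to stop using the devices, read naturally, also ends their follow-up, so the 6-month EQ-5D-5L can be lost for an intervention-related reason that applies only to the experimental arm

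*Protocol article*

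**What the plan says.** The Risk–benefit analysis section first names the event: "There is a risk that the older adults may wish to stop interacting with the technological devices". It gives dislike of one of the robots as an example. The consequence follows at once: "In this case, the experiment will be immediately stopped and terminated". The sentence does not mention questionnaires, the 6-month visit, withdrawal of consent or data already collected.

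The devices belong to one arm. The Intervention section says that "120 subjects will be enrolled in the experimental group and will receive the e-VITA platform composed of a virtual coach, several sensors for monitoring"; this arm is also given a smartphone. Of the other arm it says: "The control group will receive only the booklet with nutritional, cognitive, and physical suggestions".

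The primary endpoint in Outcome measures is quality of life, "to be measured through the EQ-5D-5L, after 6 months of training". Table 3 places EQ-5D-5L at T0 and T2 and not at T1. Sample size determination likewise assumes two assessments.

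For the analysis, the section on data collected by the researchers says: "The treatment effect on the outcome variables will be evaluated by using repeated measures ANOVA". It adds a linear regression on the change from baseline to follow-up.

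**The concern.** Stopping an intervention and leaving a trial are different events. A participant can give up the device and still answer a questionnaire at 6 months, and that answer is needed to compare the groups as randomised. The sentence in the Risk–benefit analysis appears to merge the two.

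The merger matters here for three reasons. The trigger can occur in one arm only. Its cause is the participant's reaction to the intervention, which may be related to the outcome. The primary outcome also has a single post-baseline measurement, so ending participation at any time before T2 leaves nothing for the primary comparison. A missing-data method in a later analysis plan could only model values that this rule stops anyone from collecting. It could not recover them.

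**Working it through.** **1. What is terminated.** The article uses the word *experiment* for the study as a whole in at least two places. Under Recruitment, the eligibility examination takes place before the experiment begins. Under the scales for the control group, the T2 scale asks controls how they feel after the experiment. Controls have no device, so there the word cannot mean device use. On that usage, terminating the experiment ends participation. No section says that T2 is still collected after device use stops.

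**2. Why T2 is indispensable.** With two time points, the group-by-time test in a repeated-measures ANOVA is a comparison of mean change (T2 minus T0). The regression on change uses the same quantity. A participant without T2 has no change score and enters neither analysis.

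**3. The plan's own figure.** Inputs from Sample size determination: N = 220 evaluable, m = 2 assessments, alpha 0.05, power 90%, correlation 0.5, epsilon 1, effect size 11% (f = 0.11).
- Noncentrality = f² × N × m / (1 − 0.5) = 0.0121 × 220 × 2 / 0.5 = 10.65, with 1 and 218 degrees of freedom. Power is 0.901. Solving for 90% power gives f = 0.1098, so the stated figure reproduces.
- On the change-score scale the noncentrality is delta² × N / 4. Equating the two gives delta = 4f = 0.44 SD of change.
- Dropout: 220 / 0.9 = 244.4, so 245 against the stated 240, which is within 3%. With 240 recruited and 10% lost, 216 remain and power is 0.896. The sample size is not in dispute.

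**4. The bias.** Let q be the share of the experimental arm terminated under the rule. Let D be how much lower their mean change would have been than that of those who stay.
- Mean change in the full arm = (1 − q) × stayers + q × stoppers.
- Mean change in completers = stayers.
- Difference = q × D.

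Neither q nor D is in the article, so the values below are assumptions. For the type I error column, all 120 controls are assumed observed. The last column is the actual error of a two-sided 0.05 test when there is no true effect.

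| q (number of 120) | D, SD | Bias q × D, SD | Share of 0.44 SD | Type I error |
|---|---|---|---|---|
| 5% (6) | 0.25 | 0.0125 | 3% | 0.051 |
| 5% (6) | 0.5 | 0.025 | 6% | 0.054 |
| 10% (12) | 0.25 | 0.025 | 6% | 0.054 |
| 10% (12) | 0.5 | 0.05 | 11% | 0.066 |
| 20% (24) | 0.25 | 0.05 | 11% | 0.065 |
| 20% (24) | 0.5 | 0.10 | 23% | 0.112 |

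If D is zero there is no bias. If D is negative the sign reverses and e-VITA is disadvantaged.

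**5. Power.** Without bias, power for 0.44 SD is 0.910 with 108 against 120, and 0.892 with 96 against 120. The problem is bias and not precision, so recruiting more participants would not cure it.

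**The case against.** The strongest reply is that the sentence is a reassurance in a risk section: nobody will be made to keep a device they dislike. It says nothing about data. The article is also loose with its terms. The same section uses a related word for the period of device use when it discusses participants who would like to keep the system longer. A full protocol that is not shown could contain the follow-up procedure. This stands in part. Loss of T2 is an inference and not a statement, and it should be presented as such. It does not remove the point, because the article states a rule whose more natural reading ends participation, and nothing in it points the other way.

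Several stronger readings are tempting, and the article does not support them:
- **That the control arm stays complete.** Data management gives all participants the right to withdraw, and the 10% dropout is one overall rate. Controls are only outside the reach of this particular rule.
- **That the result must lean towards e-VITA.** Nothing links disliking a robot to a worse change in EQ-5D-5L. Active people who see no need for a coach might stop too.
- **That 0.10 SD is the expected bias.** It requires 24 experimental participants to stop. That is the whole planned 10% loss in one arm, all from this cause. With loss split equally (12 per arm), the same 0.5 SD deficit gives at most 0.05 SD.
- **That the abstract contradicts Table 3.** The abstract says "Data will be collected at baseline, 3 months after the trial, and at the end of the trial, after 6 months", but other measures are taken at T1, and two EQ-5D assessments agree with Sample size determination.
- **That the lack of a mixed model is a fault.** The choice of model can be left to the analysis plan that the article announces.

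**Conclusion.** The point holds in a limited form, and the passage should be fixed. As naturally read, the rule makes the primary outcome missing for participants who reject the intervention, through a route open in the experimental arm only. A later analysis cannot retrieve those values. The size is unknown. For 5–20% stopping and a 0.25–0.5 SD worse change, the bias is about 0.01–0.10 SD, or 3–23% of the 0.44 SD design effect, with type I error between 0.051 and 0.112. At the lower end this is negligible. The conclusion rests on three things: reading the terminated experiment as trial participation, the assumed values of q and D, and control-arm loss being absent or unrelated to outcome. The direction favours e-VITA only if those who stop would have done worse. Because the loss is inferred from one sentence and both size and direction are assumed, this is a should-fix and not a fatal defect.

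**What to change.** Reconcile the Risk–benefit analysis with the 6-month endpoint in Outcome measures. Leave the participant's right to stop using the device exactly as it is; no view is taken here on when device use should end. Add that stopping device use does not by itself end outcome assessment. Such participants are still invited to the remaining scheduled assessments, including EQ-5D-5L at T2, unless they withdraw consent to follow-up, and they are analysed in the arm to which they were randomised. Device discontinuation and withdrawal from follow-up should be recorded as separate events.

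The cost is a change of wording in the protocol and consent form, and follow-up contact with a few participants who stopped. Adding EQ-5D-5L at T1 is optional: it would give a post-baseline value for people lost between T1 and T2, but none for those who leave before T1. It would not be the correction of an inconsistency.
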